### Sample size estimation

The sample size was calculated using PASS 2021 software (version 21.0.3). A two-sample independent *t*-test based on effect size was used for estimation, with cognitive function as the primary outcome. Previous studies have reported effect sizes of exercise interventions on cognitive improvement ranging from 0.54 to 2.85 [36–39]. To ensure a conservative estimation, an effect size of 0.54 for cognitive improvement was selected. With a two-sided significance level of *α* = 0.05 and statistical power of 85% (1 − *β* = 0.85), a minimum of 126 participants (63 per group) was required. To account for an anticipated 20% attrition rate, the planned recruitment target was set at 160 participants (80 per group). Due to unavoidable circumstances, such as relocation or death during the recruitment period, 156 participants were ultimately enrolled, which remained sufficient to meet the predefined statistical power requirements.

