#### Analysis of the primary outcome and secondary outcomes

The primary outcome (MoCA-B score) will be analyzed using linear mixed-effects models (LMM) within a Difference-in-Differences (DID) framework. All available time points (baseline, week 6, week 12, and week 24) will be included in the primary LMM analysis. Fixed effects will include group, time, and the group-by-time interaction, along with relevant baseline covariates (e.g., age and sex). The DID estimate corresponds to the group-by-time interaction term at week 12, representing the between-group difference in change from baseline to week 12 (the primary endpoint). Short-term (baseline to week 6), long-term (baseline to week 24), and durability effects (week 12 to week 24) will also be explored using the same framework. For secondary outcomes, continuous variables will be analyzed using similar linear mixed-effects models. Binary outcomes will be analyzed using generalized estimating equations (GEE) with a binomial family and logit link. Marginal predicted probabilities will be used to derive risk differences between groups. All analyses will be performed in the intention-to-treat (ITT) population.

Missing outcome data will be handled under the missing-at-random assumption using LMM models, which inherently accommodate incomplete repeated measurements. In addition, a sensitivity analysis will be conducted using multiple imputation with chained equations to assess the robustness of the primary results. Exploratory analyses for all outcomes will also be performed using per-protocol analyses to evaluate efficacy among participants who complete the intervention as specified and provide both baseline and 12-week outcome data. Subgroup analyses will be conducted to explore potential heterogeneity of treatment effects. Two-sided *p*-values of less than 0.05 will be considered to indicate statistical significance.

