Table 4 presents the baseline health status of participants. No significant between-group differences were detected across a range of health indicators. The health status was generally comparable between groups. Baseline values for self-rated health, MNA-SF, SPPB, PHQ-9, PSQI, ADL, frailty, social support situation, and MoCA-B were also well-balanced. Although self-rated health scores were slightly higher in the intervention group, the control group reported marginally poorer sleep quality. Cognitive function, assessed by the MoCA-B, was also similar between groups, with mean scores of 17.29 (SD = 2.32) in the intervention group and 16.74 (SD = 2.19) in the control group. Overall, these findings indicate that both randomized groups were comparable at baseline in terms of both demographic characteristics and health status, providing a sound basis for evaluating the intervention effects.

**Table 4 Tab4:** Baseline health status of participants

**Variable**	**Intervention group** (*N* = 78)	**Control group** (*N* = 78)	*χ*^2^/*F*	*P* value
**Self-rated health, mean (SD)**	71.76 (9.00)	69.50 (8.33)	2.670	0.104
**Nutritional status (MNA-SF)**			1.378	0.502
Normal nutritional status	24 (30.77)	26 (33.33)		
At risk of malnutrition	47 (60.26)	41 (52.56)		
Malnourished	7 (8.97)	11 (14.10)		
**SPPB, mean (SD)**	7.30 (2.75)	6.96 (2.86)	0.540	0.463
**Depression status (PHQ-9)**			0.289	0.591
No	58 (74.36)	55 (70.51)		
Yes	20 (25.64)	23 (29.49)		
**PSQI, mean (SD)**	11.95 (4.62)	13.46 (7.45)	2.320	0.130
**Distance vision**			2.937	0.087
Good	6 (7.69)	13 (16.67)		
Poor	72 (92.31)	65 (83.33)		
**Near vision**			6.798	0.009
Good	2 (2.56)	11 (14.10)		
Poor	76 (97.44)	67 (85.90)		
**Hearing**			0.880	0.348
Good	7 (8.97)	4 (5.13)		
Poor	71 (91.03)	74 (94.87)		
**ADL score, mean (SD)**	21.32 (7.08)	22.31 (7.58)	0.710	0.402
**Frailty status (FP)**			1.354	0.245
No	61 (78.21)	65 (83.33)		
Yes	17 (21.79)	13 (16.67)		
**Limited social network**			0.104	0.747
No	35 (44.87)	33 (42.31)		
Yes	43 (55.13)	45 (57.69)		

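### The primary mixed model leaves the arms' baseline MoCA-B means free to differ, so it is in effect a change-score analysis: valid, but less precise than a baseline-adjusted model and shifted given the observed 0.55-point gap

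*Protocol article*

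**What the plan says.** Under Analysis of the primary outcome and secondary outcomes, the protocol article places the primary mixed model in a difference-in-differences (DID) framework and fixes three features of it.

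- Baseline is a response: "All available time points (baseline, week 6, week 12, and week 24) will be included in the primary LMM analysis".
- The arms may differ at baseline, because group enters as a main effect: "Fixed effects will include group, time, and the group-by-time interaction, along with relevant baseline covariates (e.g., age and sex".
- The primary estimate is the week-12 interaction: "The DID estimate corresponds to the group-by-time interaction term at week 12, representing the between-group difference in change from baseline to week 12".

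Baseline MoCA-B is not named as a covariate, and no common baseline mean is imposed. Continuous secondary outcomes get models of the same kind. The section Primary outcome measures promises adjusted mean differences without saying that they are adjusted for the baseline score.

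The baseline result is already published, "with mean scores of 17.29 (SD = 2.32) in the intervention group and 16.74 (SD = 2.19) in the control group", and Table 4 gives F = 2.320, p = 0.130.

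**The concern.** The arms were randomised 1:1 after the baseline assessments, so their expected baseline means are equal. A free group term spends information on estimating a difference that is zero in expectation. It also subtracts the whole of any chance gap from the week-12 difference, although only the part predicted by the slope of week-12 on baseline score is expected to persist.

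At stake are the width of the primary confidence interval and, for this particular randomisation, where the estimate is centred. The same model form passes to every continuous secondary outcome.

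**Working it through.** **Inputs.** Baseline MoCA-B of 17.29 (SD 2.32) and 16.74 (SD 2.19), 78 per arm (Table 4). Model terms and estimate as given in the analysis section. Neither the baseline to week-12 correlation ρ nor the week-12 SD is in the article, so both are assumptions here, shown over a range.

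**1. The article's own baseline figure.** Gap = 17.29 − 16.74 = 0.55. Pooled SD = √((2.32² + 2.19²)/2) = 2.256. Standard error = 2.256 × √(2/78) = 0.361. F = (0.55/0.361)² = 2.32, p = 0.130, which agrees with Table 4. The gap is 0.55/2.256 = 0.24 SD.

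**2. What the model estimates.** With categorical time, a free group term and complete data, the week-12 interaction is (intervention week 12 − intervention baseline) − (control week 12 − control baseline). In one simulated complete data set with four visits and with age and sex in the model, the interaction was 0.5893 and the raw difference in mean change was also 0.5893. Covariates entered as main effects do not alter it. With missing visits the identity is approximate.

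**3. Formulas.** Let k be the week-12 SD divided by the baseline SD, and take variances in units of the baseline variance.

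- Change score: 1 + k² − 2ρk
- Baseline-adjusted: k²(1 − ρ²)
- Slope of week 12 on baseline: ρk
- Shift given the observed gap: −(1 − ρk) × 0.55

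For k = 1 the variances are 2(1 − ρ) and 1 − ρ², so their ratio is (1 + ρ)/2.

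**4. Results.**

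| k | ρ | slope | variance ratio, adjusted/DID | saving | shift (points) |
|---|---|---|---|---|---|
| 1 | 0.5 | 0.50 | 0.75/1.00 = 0.75 | 25% | −0.28 |
| 1 | 0.7 | 0.70 | 0.51/0.60 = 0.85 | 15% | −0.17 |
| 1 | 0.8 | 0.80 | 0.36/0.40 = 0.90 | 10% | −0.11 |
| 1.25 | 0.5 | 0.625 | 1.172/1.3125 = 0.893 | 11% | −0.21 |
| 1.25 | 0.7 | 0.875 | 0.797/0.8125 = 0.981 | 2% | −0.07 |
| 1.25 | 0.8 | 1.00 | 0.5625/0.5625 = 1.00 | 0% | 0.00 |
| 1.5 | 0.8 | 1.20 | 0.81/0.85 = 0.953 | 5% | +0.11 |

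The rows with k above 1 matter here. Under Recruitment and eligibility, entry requires a MoCA-B score within education-specific bands, which restricts the spread at baseline but not at week 12.

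**5. Missing visits.** Simulation with the gap fixed at +0.55, equal SDs, ρ = 0.6, about 20% dropout and 150 runs: the published model averaged 0.98 and the common-baseline model 1.20, for a true value set at 1.22. The difference of 0.22 equals (1 − 0.6) × 0.55. Mean standard errors were 0.351 and 0.321, a variance ratio of (0.321/0.351)² = 0.84, so a saving of about 16% against 20% with complete data.

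**The case against.** The strongest case for the published model is that nothing in it is invalid. The endpoint is defined as a between-group difference in change, and the model estimates exactly that. Under 1:1 randomisation the estimator is unbiased and its type I error is controlled. All of this stands.

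A reader might infer that the analysis is biased against the intervention. The documents do not support that as a general statement. The shift exists only given one chance gap (p = 0.130), it disappears at slope 1, and it changes sign above that. Nor does the gap suggest that randomisation failed.

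Two further readings are tempting. The first expresses the shift as a share of a planned effect in MoCA-B points. The article plans no such effect: it states only that "an effect size of 0.54 for cognitive improvement was selected", a standardised value. The second is that the stated 85% power holds only if ρ is at least 0.5. That would follow only if 0.54 is in raw-score SD units, and the section Sample size estimation does not say which SD is meant. If it is the SD of change, the planned t-test matches a change-score analysis at any ρ. The sample size itself reproduces: effect size 0.54, two-sided 5% and 85% power give 62.6, hence 63 per group. It is not in dispute.

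The last objection is timing. Recruitment was expected to end by March 2025, the last assessment falls at weeks 24–25, and the article appeared in March 2026. Follow-up may therefore be complete, and replacing the primary estimator now could look driven by the data. This stands, and it limits when and how the change may be made.

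**Conclusion.** The point holds as one of efficiency and of a conditional shift, not of validity. The article fixes an estimator that ignores what randomisation guarantees about the baseline means, and the open covariate list does not rescue it because baseline is already a response. Adjusting for baseline is never less precise in large samples.

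The size is uncertain. Over the range examined, the variance saving runs from 25% (equal SDs, ρ = 0.5) to nothing at slope 1, and the shift from −0.28 points through zero to slightly positive when the slope exceeds 1. These figures rest on an assumed ρ and an assumed ratio of week-12 to baseline SD. The change is worth making, but the trial's conclusions would not be unsound without it.

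**What to change.** In the statistical analysis plan to be signed before database lock, and before any unblinded outcome data are seen, specify a constrained longitudinal model for MoCA-B: a common baseline mean for both arms, categorical time, group-by-time terms at weeks 6, 12 and 24, and an unstructured within-person covariance. Equivalently, use the post-baseline scores as responses, with baseline MoCA-B and its interaction with visit as covariates.

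Keep the week-12 contrast as the primary estimate and use the same form for continuous secondary outcomes. Report the published DID model as a sensitivity analysis.

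Date the change and justify it by general efficiency in a randomised design, not by the direction of the observed gap. If outcome data have already been seen, keep the DID model as primary and add the baseline-adjusted model as a sensitivity analysis.

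The cost is one model specification and a dated, documented departure from the published article. No further data are needed.

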### Statistical analysis plan

Statistical analyses will be undertaken by an independent statistician, according to a statistical analysis plan developed and signed before database lock. All analyses will use STATA/MP 17.0 or a later version if available.

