#### Summary of trial flow and baseline characteristics

Participant flow through the trial will be documented using a CONSORT diagram. The baseline characteristics will be described using summary statistics. Baseline demographic and clinical characteristics will be summarized by group and overall. Continuous variables will be described using means and standard deviations (SD) or medians and interquartile ranges (IQR), as appropriate, while categorical variables will be presented as frequencies and percentages. Baseline values for each outcome variable will be reported at different time points. Comparisons between participants who complete follow-up and those lost to follow-up will be conducted using independent t-tests and chi-square tests to evaluate potential bias.

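### The missing-at-random handling through the LMM does not extend to the binary secondary outcomes analysed by GEE, and the only robustness check on the primary result shares the LMM's assumption

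*Protocol article*

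**What the plan says.** All of this is in the protocol article, mostly under Analysis of the primary outcome and secondary outcomes.

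- **Missing data:** "Missing outcome data will be handled under the missing-at-random assumption using LMM models, which inherently accommodate incomplete repeated measurements".
- **Primary model:** "All available time points (baseline, week 6, week 12, and week 24) will be included in the primary LMM analysis". Continuous secondary outcomes get similar mixed models.
- **Binary outcomes:** "Binary outcomes will be analyzed using generalized estimating equations (GEE) with a binomial family and logit link", and then "Marginal predicted probabilities will be used to derive risk differences between groups". No weighting, imputation or working correlation is given for them.
- **Robustness:** "a sensitivity analysis will be conducted using multiple imputation with chained equations to assess the robustness of the primary results". No analysis under departures from MAR is named.
- **Descriptive check** (Summary of trial flow and baseline characteristics): "Comparisons between participants who complete follow-up and those lost to follow-up will be conducted using independent t-tests and chi-square tests".
- **Expected loss** (Sample size estimation): 20% attrition.
- **Status of the analysis plan** (Statistical analysis plan): analyses are to run "according to a statistical analysis plan developed and signed before database lock". That plan is not shown.

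**The concern.** Two separate weaknesses follow from what the article fixes.

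**Binary outcomes.** A mixed model fitted by likelihood uses each participant's earlier measurements through the joint distribution of the visits, so dropout that depends on those measurements can be ignored. Ordinary unweighted GEE has no such general property. Its consistency is guaranteed when data are missing completely at random or when missingness depends only on covariates in the model. The stated MAR handling is tied to the LMM and the imputation to the primary results, so no stated method covers the outcomes reported as intention-to-treat risk differences.

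**Primary outcome.** Standard chained-equations imputation assumes MAR, as the LMM does. If residents who decline or fall ill miss visits because of their unobserved state, both analyses move in the same direction. Close agreement could then be read as robustness to informative loss when that has not been examined.

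Dropout that differs by arm is plausible. Participants are unblinded, and the dropout rules in Process evaluation are defined by training attendance, which applies only to the intervention arm.

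**Working it through.** **1. The plan's own figures.** With a standardised effect of 0.54, two-sided alpha 0.05 and a two-sample t-test, the noncentral t gives 85.25% power at 63 per group and 84.68% at 62. The stated 126 is reproduced. 126 / 0.8 = 157.5, so 158 are needed and the planned 160 covers it. Neither part of this point changes the sample size. At 20% attrition, 0.20 × 78 = 15.6 participants per arm would lack week-12 data.

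**2. Binary outcome under MAR dropout.** Not in the documents, hence assumed: latent correlation 0.7 between visits (exchangeable or autoregressive), 19% to 21% missing by week 12, and dropout driven by the previous observed outcome. Each scenario had 6,000 simulated participants. Bias is the GEE risk difference minus the full-data one.

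| Latent structure | Dropout mechanism | Full data | GEE, independence (bias) | GEE, exchangeable (bias) |
|---|---|---|---|---|
| Exchangeable | same in both arms | -0.083 | -0.090 (-0.007) | -0.089 (-0.006) |
| Exchangeable | intervention arm only | -0.078 | -0.115 (-0.037) | -0.077 (+0.001) |
| Exchangeable | opposite by arm | -0.064 | -0.116 (-0.052) | -0.066 (-0.002) |
| Autoregressive | same in both arms | -0.096 | -0.094 (+0.002) | -0.094 (+0.002) |
| Autoregressive | intervention arm only | -0.083 | -0.111 (-0.028) | -0.082 (+0.001) |
| Autoregressive | opposite by arm | -0.089 | -0.129 (-0.040) | -0.087 (+0.002) |

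Material bias, 2.8 to 5.2 percentage points, needed both an independence structure and dropout that differed by arm. With an exchangeable structure and arm-specific dropout the estimate stayed within 0.002 of the full-data value.

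**3. Continuous outcome: likelihood against imputation.** Assumed: SD 2.3 (baseline SDs in Table 4 are 2.32 and 2.19), correlation 0.6 between visits, 17% to 21% missing at week 12, and lower scorers in the intervention arm more likely to drop out. The true difference in change was (18.5 − 17) − (17.3 − 17) = 1.2. Three runs of 10,000; an unstructured-normal likelihood fit stands in for the LMM, and imputation was done by arm with the same variables.

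| Dropout depends on | Full data | Likelihood | Chained equations |
|---|---|---|---|
| previous observed score (MAR) | 1.200 | 1.195 | 1.201 |
| current unobserved score (not MAR) | 1.200 | 1.335 | 1.330 |

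When MAR fails, the errors are 1.335 − 1.200 = 0.135 and 1.330 − 1.200 = 0.130, about 11% of the true effect. The two methods differ from each other by only 0.005.

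**4. What a delta analysis would show.** If the 20% missing in the intervention arm were truly 1 to 2 points worse than MAR predicts, the effect is overstated by 0.20 × 1 = 0.2 to 0.20 × 2 = 0.4 points. The protocol gives no raw target difference. One can be derived from the baseline SDs: pooled SD = √((2.32² + 2.19²)/2) = 2.26, and 0.54 × 2.26 = 1.22 points. On that derived scale the overstatement is 0.2/1.22 = 16% to 0.4/1.22 = 33%.

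**The case against.** The best defence has four parts.

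- **The missing-data sentence is correct as written.** It ties MAR to the LMM and never claims that the GEE is valid under MAR. This stands: a reader might infer that the plan fails to deliver its stated handling, but for the primary and continuous secondary outcomes it does deliver it.
- **Much of the detail belongs in the signed analysis plan.** Working correlation, imputation model and any further sensitivity analysis are commonly left there, and their absence from an article is not a fault in itself. This stands. However, the article does commit to GEE for binary outcomes, to MAR handling through a model those outcomes do not use, and to one robustness check with the same assumption. A plan that followed this text without adding to it would inherit both weaknesses.
- **The size of the bias is easily overstated.** A reader might argue that if true frailty is 25% in both arms and the 20% of controls who are lost are 50% frail, observed controls show (0.25 − 0.20 × 0.50)/0.80 = 18.75%, a 6.25-point bias. That is a raw proportion among those observed. It gives a repeated-measures GEE no credit for earlier visits, and it exceeds every bias in the simulations. Likewise, calling the GEE simply invalid goes too far, given the exchangeable results.
- **Imputation is not an empty check.** A reader might infer that it must reproduce the LMM. The article specifies no imputation model and does not say that imputation tests departures from MAR; auxiliary variables could make the assumption weaker and the answer different. The near-identity shown above holds when the same variables are used.

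The article also has dropouts encouraged to complete follow-up, so leaving the programme need not mean missing data, and it compares completers with those lost. Neither step, nor the per-protocol analysis that requires week-12 data, relaxes MAR for the intention-to-treat effect.

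**Conclusion.** The point holds in limited form. The LMM under MAR is a sound primary analysis and nothing here undermines it. What is weak is the cover for binary secondary outcomes and the reach of the single robustness check.

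For binary outcomes, validity under MAR is not assured by the stated method. The bias could be about 3 to 5 percentage points in a risk difference or negligible, depending on a working correlation that is not stated and on whether dropout differs by arm. For the primary result, agreement between the LMM and standard imputation would not be evidence against informative loss. In the assumed scenario both were wrong by about 0.13 points and agreed with each other.

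All these magnitudes rest on assumed correlations, dropout mechanisms and about 20% missing. They show what can happen and do not predict this trial's bias. The 1.22-point effect is derived from baseline SDs and is not a protocol figure.

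**What to change.** 1. **Binary secondary outcomes.** State one method that is valid under MAR: run the GEE on multiply imputed data, imputed separately by arm and using earlier visits; or use inverse-probability-weighted GEE; or fit a mixed logistic model and obtain risk differences by marginal standardisation. Name the working correlation if GEE is kept.
2. **Week-12 MoCA-B.** Keep the LMM and the chained-equations imputation. Add a sensitivity analysis under missing not at random: either delta-adjusted imputation over a prespecified range, reporting the shift at which the conclusion changes, or a reference-based imputation. Describe the existing imputation as a check within MAR.

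Both changes can go into the analysis plan before it is signed. They cost some wording and a modest amount of extra analysis, with no new data and no change to sample size. With 78 per arm, by-arm imputation models for uncommon binary outcomes will have to be kept small.

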### Study design, setting, and participants

This MIND-STEP study is a superiority, single-blind, parallel-group randomized controlled trial designed in a 1:1 ratio to evaluate the effectiveness of a multicomponent exercise intervention among MCI older adults residing in a nursing home in China. The trial design and timeline are summarized in Fig. 1 and Table 1. Ethics approval was granted by the Medical Ethics Committee of Huzhou Third People’s Hospital and was registered (trial registration number ChiCTR2400088301). Participants will be randomly assigned in a 1:1 ratio to either an intervention group receiving 12 weeks of a multicomponent exercise program or a control group receiving usual care with no structured exercise intervention. Assessors responsible for performing the baseline (week 0), midline (week 6–7), endline (week 12–13), and follow-up assessments (weeks 24–25, corresponding to approximately 12–13 weeks post-intervention) will be blinded to allocation.

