### Intervention

#### Intervention group

Participants in the intervention group will receive a 12-week, group-based multicomponent exercise program to be delivered through in-person, face-to-face sessions. Each session will last 30 min and will be conducted twice per week. The multicomponent exercise intervention will consist of five structured components: a warm-up, aerobic training, resistance training, mind–body training, and a cool-down period, forming a complex, theory-informed approach tailored to the physical and cognitive needs of older adults. Participants will be guided by nurses in the nursing home to perform aerobic training, resistance training, and dual-task (mind–body) training throughout the 30-min session. A Rate of Perceived Exertion (RPE) of 5–6, corresponding to moderate intensity, will be recommended. Core aerobic exercises will include shoulder movements, hip abduction or extension, and thigh lifts. Resistance training will consist of functional movements such as squats and trunk twists. Mind–body training will incorporate coordinated activities such as seated marching combined with attention tasks and standing marching paired with inhibition tasks. All participants will be instructed to complete a brief warm-up at the beginning and a cool-down routine at the end of each session to promote safety and recovery.

The intervention will feature a group-based multicomponent exercise program and will be conceptually grounded in the integrated HAPA-TPB model. This theoretical framework was selected to address known facilitators and barriers to exercise engagement among older adults [23], as it incorporates both the motivational phase (e.g., intention formation) and the intenders phase (e.g., planning, execution, maintenance of behavior) and action phase, thereby providing a comprehensive framework for promoting sustainable health behavior change in later life. This integrated model combines the stage-based behavioral pathway of HAPA (preintenders, intenders, and actors) [24, 25] with key motivational determinants from TPB, including attitudes, subjective norms (operationalized as social support in this study), and perceived behavioral control [26]. Particular emphasis was placed on enhancing self-efficacy and peer-based social support as core mechanisms to strengthen adherence and sustain exercise behavior.

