### Measurements

#### Primary outcome measures

All outcome data will be collected through a face-to-face electronic questionnaire system administered by trained physicians or nurses who have received standardized training. The primary outcome is cognitive function measured by the Montreal Cognitive Assessment-Basic (MoCA-B) score. The MoCA-B is a validated screening tool specifically developed to detect mild cognitive impairment (MCI) in individuals with limited educational backgrounds or illiteracy [27, 28]. It evaluates a range of cognitive domains, including executive function, immediate and delayed recall, verbal fluency, orientation, calculation, abstraction, visuoperception, and naming. The assessment takes approximately 15 min to complete and is scored out of a maximum of 30 points. To reduce potential bias related to education and literacy, one point will be added to the total score for participants with fewer than 4 years of education or those identified as illiterate (defined as the inability to read or write fluently in daily life), provided their raw score is below 30.

MoCA-B will be assessed at baseline, 6 weeks, 12 weeks, and 24 weeks post-randomization. The primary endpoint is defined as the between-group difference in change from baseline to 12 weeks post-randomization (end of the intervention period). Results will be presented as adjusted mean differences with 95% confidence intervals. All primary analyses will follow the intention-to-treat principle.

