#### Process evaluation

A comprehensive process evaluation will be conducted to assess the quality of intervention implementation and its potential impact on study outcomes. This evaluation will address the following dimensions: Eligibility and recruitment will be tracked using data on the proportion of eligible participants, recruitment and retention rates, and reasons for drop-off. Intervention acceptability will be evaluated through supervisory documents, adherence records and satisfaction surveys [35]. Adherence will be measured based on the number of dropouts and session frequency across groups. Participants will be classified as having dropped out if they meet any of the following criteria: average training frequency of ≤ 2 times per week over 3 weeks; average frequency of ≤ 1 time per week for two consecutive weeks; or no sessions completed within a 1-week period. Temporary absences of 1–2 weeks due to medical treatment or personal reasons will be exempt if participants resume full participation thereafter. All dropouts will be encouraged to complete follow-up assessments.

Outcome acceptability will be assessed by calculating the completion rates of outcome questionnaires at baseline, 6 weeks, and 12 weeks. Adverse events, including falls, fractures, muscle strains, cardiovascular events, and new or exacerbated musculoskeletal, cardiovascular, or metabolic conditions, will be monitored throughout the study. Participants in the intervention group will be asked about any adverse events following each session. All reported events will be documented and the responsible authorities will be notified promptly, and relevant free examinations and management strategies will be provided within the nursing home or referred to the appropriate medical institution. Participants experiencing minor adverse events may continue with the study if the participants’ condition does not worsen and if adequate rest and treatment do not interfere with ongoing participation.

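### The exploratory per-protocol analysis is said to evaluate efficacy, but completing the intervention can select only in the exercise arm, so the contrast can be non-null without any effect

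*Protocol article*

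**What the plan says.** The section on analysis of the primary and secondary outcomes states: "Exploratory analyses for all outcomes will also be performed using per-protocol analyses to evaluate efficacy". The set is restricted to "participants who complete the intervention as specified and provide both baseline and 12-week outcome data". The same section sets a two-sided 0.05 threshold and does not exempt exploratory analyses from it.

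The comparator, in the study design section, is "a control group receiving usual care with no structured exercise intervention". The control group subsection describes basic, nutritional and safety care, and nothing that a participant could complete.

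On the main analysis, the primary outcome section says "All primary analyses will follow the intention-to-treat principle". The analysis section goes further, with "All analyses will be performed in the intention-to-treat (ITT) population", one paragraph before it introduces the per-protocol analyses.

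The process evaluation says: "Adherence will be measured based on the number of dropouts and session frequency across groups". Its numeric criteria count training sessions only. One of them classes as a dropout anyone with an "average training frequency of ≤ 2 times per week over 3 weeks", while the intervention section says of the programme: "Each session will last 30 min and will be conducted twice per week".

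**The concern.** A per-protocol comparison keeps some protection from randomisation only if similar people are removed from both arms. Here the completion filter works on one side. Exercisers who stop attending leave the set; the controls who would have stopped, had they been offered sessions, stay in.

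The article itself gives reason to expect that stayers differ. Its intervention section and Table 2 name loss of motivation, apathy, fatigue and joint pain as barriers to participation. The process evaluation allows for absences for medical treatment. The trial-flow section plans to compare people lost to follow-up with those retained, to look for bias. Any of these features may go with the course of MoCA-B over 12 weeks.

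At stake is the reading of an exploratory result. Presented as efficacy, it will be taken as the effect of doing the exercise, although it mixes that effect with the difference between people who stay and people who stop.

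**Working it through.** **1. The plan's own figure.** The article gives no figure for the per-protocol analysis; its only design calculation is the sample size (d = 0.54, two-sided 0.05, power 85%, 20% attrition). Normal approximation: n = 2(1.960 + 1.036)²/0.54² = 17.957/0.2916 = 61.6, so 62 per group. With the noncentral t, power is 84.7% at 62 and 85.3% at 63 per group, so the stated 63 is reproduced. Attrition: 63/0.8 = 78.75, so 79 per group or 158, close to the target of 160. This point does not affect the sample size.

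**2. Which criterion acts in which arm.**

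| Criterion | Exercise arm | Usual-care arm |
|---|---|---|
| Baseline and week-12 data | applies | applies |
| Completed the intervention | applies | no content: no sessions offered |

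**3. Bias with no treatment effect.** From the article: 78 per arm, two-sided 0.05. Assumed, because the documents do not give them: the correlation r between latent attendance and change in MoCA-B, and the proportion q of the exercise arm counted as completers. Change is standard normal in both arms, the most adherent fraction q of the exercise arm is kept, all controls are kept, and a two-sample t-test is applied. The expected bias in SD units of change is

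bias = r·φ(z)/q, with z = Φ⁻¹(1 − q).

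For q = 0.8, z = −0.842 and φ(z) = 0.2800, so r = 0.3 gives 0.3 × 0.2800/0.8 = 0.105 SD, or 0.105/0.54 = 19% of the planned effect. If the SD of change equalled the baseline SD of about 2.25 (the article reports 2.32 and 2.19 at baseline and no SD of change), this would be about 0.24 MoCA-B points.

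Bias in SD, with the simulated false-positive rate in brackets (20,000 trials per cell):

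| r | q = 0.9 | q = 0.8 | q = 0.7 | q = 0.6 |
|---|---|---|---|---|
| 0 | 0 (5%) | 0 (5%) | 0 (5%) | 0 (5%) |
| 0.1 | 0.019 (5.2%) | 0.035 (5.1%) | 0.050 (5.9%) | 0.064 (6.0%) |
| 0.2 | 0.039 (5.5%) | 0.070 (6.6%) | 0.099 (8.6%) | 0.129 (10.5%) |
| 0.3 | 0.058 (6.3%) | 0.105 (9.4%) | 0.149 (13.4%) | 0.193 (18.1%) |
| 0.4 | 0.078 (7.5%) | 0.140 (13.4%) | 0.199 (20.1%) | 0.258 (28.8%) |

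**4. Is the one-sidedness the cause?** Applying the same latent selection to both arms at q = 0.8 (6,000 trials each) gives bias of essentially 0 and a false-positive rate of 5.7% at r = 0.3 and 4.6% at r = 0.5. The inflation therefore comes from selecting in one arm only.

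**5. The dropout rule.** A participant who attends every session averages exactly 2 per week (24 sessions over 12 weeks), which satisfies the dropout criterion of 2 or fewer per week over 3 weeks. The two statements cannot both stand as written.

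**The case against.** The analysis is labelled exploratory. The primary and secondary analyses are intention-to-treat, and multiple imputation is the named sensitivity analysis for the primary result. This stands in full. A reader might infer that the trial's main conclusion is exposed, or that its handling of missing data is weakened; the article supports neither.

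Which controls enter a per-protocol set is ordinary content for the separate signed analysis plan, which is not shown. This also stands: the missing control-arm rule is not by itself a fault. A reader might infer that the wording excludes every control, but that would leave nothing to compare and is not a plausible intention. What remains is what the article does state: a completion rule with content in one arm, and a stated purpose of evaluating efficacy.

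The size depends on r and q, neither of which is documented. That is right. The problem nearly vanishes at r = 0.1 or with 90% completers, and the 20% attrition figure is only a proxy for non-completion. The check is also an unadjusted t-test, whereas the main model carries baseline covariates; r is best read as the correlation left after adjustment.

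A reader might take the process-evaluation dropout rule as the definition of a completer and conclude that the exercise-arm set would be empty. The analysis section does not refer to that rule, so the link is an inference. The conflict between the rule and the schedule is real but separate.

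Finally, a complier-average estimate has its own assumption, that assignment acts only through attendance. This is open to doubt here: participants are unblinded, and the programme includes education, planning, peer modelling and staff encouragement. With a yes/no threshold, people below it still receive some sessions, so the estimate can be too large. This argues against treating it as assumption-free and against a threshold as the main exposure.

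**Conclusion.** The concern holds in limited form. As worded, the per-protocol contrast compares exercisers selected on completion with controls not selected in the same way, and efficacy is too strong a word for it. Whether it misleads depends on attendance being prognostic, which the article makes plausible but does not quantify. Over the assumed range (r 0.1–0.4, 60–90% completers, 78 per arm, no effect) the bias is about 0.02–0.26 SD and the false-positive rate runs from about 5% to 28–29%. The case nearest to a documented figure, 80% completers with r = 0.3, gives 0.105 SD and 9–10%. These are illustrations, not predictions for this trial. The point deserves a change because the remedy is cheap and uses data the trial already plans to record; the intention-to-treat result does not depend on it.

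**What to change.** 1. For the effect of attending on week-12 MoCA-B, pre-specify a complier-average causal effect with randomised arm as the instrument. Keep all randomised participants, adjust for baseline MoCA-B, age and sex, and use multiple imputation for missing week-12 values. The main exposure is sessions attended out of 24 (12 weeks × 2), with controls at zero. As a sensitivity analysis, use one pre-stated attendance threshold; this is essentially the intention-to-treat effect divided by the attending proportion (a factor of 1/0.8 = 1.25 at 80%).
2. State the downsides alongside it: a wider interval, linearity in the number of sessions for the dose version, and the assumption that assignment acts only through attendance, which is weaker for the threshold version.
3. Keep any per-protocol table as supportive and non-randomised, drop the word efficacy, and state which controls enter. Reword the sentence placing all analyses in the intention-to-treat population so that it allows for this exception.
4. Separately, reconcile the twice-weekly schedule in the intervention section with the dropout criteria in the process evaluation before any completer set is formed.

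The cost is a paragraph in the analysis plan, which need only be signed before database lock, and one extra model with its threshold variant on attendance records that are already planned.
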